# Freezing of gait and the effects of vibrotactile cueing in Parkinson’s disease–a study protocol of a cross-sectional multimodal brain imaging approach in virtual walking scenarios

**DOI:** 10.3389/fnins.2026.1872933

**Published:** 2026-07-09

**Keywords:** electroencephalography, external cueing, functional near-infrared spectroscopy, gait disorders, neurorehabilitation, Parkinson, treadmill walking, virtual reality

## Abstract

**Background:**

Freezing of gait (FOG) is one of the most debilitating motor symptoms in Parkinson’s disease (PD), affecting a substantial proportion of people with PD. Numerous hypothetical mechanisms exist, attempting to explain FOG. Current evidence originated from stationary measures in lying positions, limiting the understanding of neurophysiological changes elicited by FOG episodes during regular locomotion. Neurophysiological aspects of FOG, especially in response to vibrotactile cueing, have been explored only by a few studies. To address this gap, the current study aims to investigate FOG episodes in people with PD and the impact of vibrotactile cueing while walking through virtual environments on a self-paced treadmill.

**Methods:**

Thirty people with Parkinson’s Disease and FOG will be recruited. They will undergo screening and familiarization before performing different walking tests in virtual reality using the Gait Real-time Analysis Interactive Lab (GRAIL). Participants will perform two experimental blocks, each consisting of four walking trials of approximately 10 min. A break of 10 to 30 min will be provided between blocks. Walking with or without vibrotactile cueing will be performed in alternation. During walking, electrocortical (EEG), hemodynamic (fNIRS), kinematic data (3D motion capture), and kinetic data (force plates) will be recorded. Data will be analyzed to investigate spatiotemporal and frequency characteristics of electrocortical and hemodynamic brain activity related to FOG and the impact of vibrotactile cueing on neural signatures and gait improvements in FOG.

**Discussion:**

Combining neurophysiological measurements of EEG and fNIRS paired with kinematics and kinetics will provide insights into the cortical and behavioral changes associated with FOG and vibrotactile cueing, to derive results that can be used for the design of intervention strategies for treating PD.

**Study protocol registration:**

https://drks.de/search/de/trial/DRKS00034584, identifier DRKS00034584.

## Introduction

1

James Parkinson’s “An Essay on the Shaking Palsy” (1817) introduced the first formal medical description of Parkinson’s disease (PD), which today is one of the most common neurodegenerative disease worldwide. During recent decades, PD has been on the rise, with nearly 1 million people being affected by PD in the US alone, and this number is expected to rise to 1.2 million by 2030 (Marras et al., 2018). People with PD suffer from a wide range of motor symptoms, including tremors, muscle rigidity, bradykinesia, and postural instability (Giladi et al., 2001; Nutt et al., 2011). One of the most debilitating motor symptoms of the disease, however, is freezing of gait (FOG), of which approximately 60% of people with PD are suffering during the course of their disease (Macht et al., 2007; Zhang et al., 2021). FOG is described as a sudden and temporary inability to move forward. FOG manifests as either small steps in a forward shuffling motion, alternating trembling of the legs on site with a frequency of about 3–8 Hz, or akinesia (Hausdorff et al., 2003; Moore et al., 2008; Schaafsma et al., 2003). Typical triggers for FOG can be categorized as movement-related, cognition-related or emotion-related. Movement-related triggers of FOG include turnings, passing through (narrow) doorways or passages, and gait initiation (Cockx et al., 2023; Palmisano et al., 2022; Spildooren et al., 2019). Cognition and emotion-related FOG triggers, in turn, typically refer to situations with increased cognitive load or higher levels of anxiety (Martens et al., 2016; Pimenta et al., 2019; Spildooren et al., 2010). Unfortunately, the underlying neural mechanisms and pathways of FOG remain largely unclear, and current treatment options, such as dopaminergic medication and deep brain stimulation, often remain ineffective, particularly in resolving FOG. Given these challenges, so-called cueing strategies have emerged as effective alternatives to reduce FOG during daily life activities, among which vibrotactile cueing seems to be particularly promising. In this study, we will explore the neurophysiological correlates of FOG and assess the efficacy of vibrotactile cueing as a potential intervention to alleviate this debilitating symptom.

Recent reviews have summarized hypothetical neural pathways for the generation of FOG that include (i) interference between the basal ganglia (BG) and supplementary motor area (SMA), (ii) deficient crosstalk between BG, SMA and other cortical areas, (iii) interference between BG and frontal lobe, (iv) disruption along the dorsal visuomotor stream, and (v) uncoupling between SMA and motor cortex (Bardakan et al., 2022; Marquez et al., 2020; Nutt et al., 2011). Notably, these hypotheses and models share common but also unique (neural) pathways and mechanisms, supporting both the complexity and heterogeneity of the observed phenology of FOG, but also the idea of a common key process in the motor control circuit that ultimately triggers FOG. However, these neural mechanisms assumed to underlie FOG are predominantly based on stationary measurements, using gait imagery or stepping tasks in MRI laboratories. This contrasts with the dynamic nature of gait and FOG, creating a gap between experimental setups and real-world conditions. Recent advancements in ambulatory assessments, e.g., using mobile EEG / fNIRS during walking, now allow the investigation of FOG under more realistic, everyday-like conditions.

A few mobile EEG studies have investigated the electrocortical correlates associated with FOG in Timed Up-and-Go (TUG) tasks. They consistently found increased theta activity in right parietal and central brain regions during FOG episodes and during transition to FOG, suggesting an association of FOG with misguided integration of sensory information (Cao et al., 2021; Handojoseno et al., 2012, 2013; Shine et al., 2014). In addition, increased beta synchronization across the central cortex has been reported during FOG as well as an increase in beta activity across the parietal cortex along with changes in fronto-central beta coherence during transition to FOG (Handojoseno et al., 2015b; Shine et al., 2014). A surge in beta activation has been shown to be associated with motor symptoms in PD (Morelli and Summers, 2023) and is suggested to indicate impaired transmission of motor plans from frontal areas to the motor cortex (Shine et al., 2014). Additionally, investigating the differences between voluntary stopping and FOG, Cao et al. (2021) noted diminished power and different low-beta and delta power patterns in central regions during voluntary stopping compared to FOG (Cao et al., 2021). They also reported increased theta and alpha power over central and occipital regions during FOG compared to transition to FOG. Another study by Cockx et al. (2023) using fNIRS during walking showed a decrease in prefrontal cortex (PFC) activity during FOG compared to voluntary stopping (Cockx et al., 2024). Furthermore, they reported higher activation in the SMA and premotor cortex (PMC) in freezers compared to age-matched healthy controls during turning, stopping and walking through doorways. They emphasize the influence of the SMA in the pathophysiology of FOG and propose that FOG might emerge as a result of a disbalance between SMA and PFC. Moreover, connectivity analysis revealed increased coherence between central and frontal regions in the theta band during FOG, along with changes in theta synchronization during transition to FOG (Handojoseno et al., 2013; Shine et al., 2014). In this vein, Maidan et al. (2015) also reported an increased hemodynamic activation (fNIRS) in the frontal lobe before and during FOG (Maidan et al., 2015). However, these alterations were only observed in anticipated turns, indicating involvement of executive control mechanism in FOG; in line with the executive dysfunction hypothesis (Bardakan et al., 2022). Other important findings include intensified brain network synchronization with longer disease progression, which was consistently observed across various frequency bands (Asher et al., 2021). These results of increased coherence between frontal and central brain regions as well as increased network synchronization with increased disease severity potentially indicate the presence of compensatory neural mechanisms aimed at maintaining gait performance comparable to healthy controls (Poston et al., 2016).

In summary, previous studies have identified higher beta and theta power, higher synchronization and lower or higher hemodynamic brain activation in frontal and central regions during FOG or during transition to FOG. These findings are mainly based on modified versions of TUG tasks, providing limited transfer to more everyday-life walking conditions. Further, previous studies used either EEG or fNIRS, rather than employing a multimodal approach. The investigation of walking in VR and the simultaneous recording of EEG and fNIRS may increase the ecological validity and will allow to further understand the neurophysiology of FOG in PD. Understanding the neurophysiological correlates underlying FOG is crucial for the development and evaluation of effective intervention methods to ameliorate FOG in daily life.

Various approaches have been shown to be effective in counteracting the symptoms of PD, including FOG. Levodopa remains the most common medical treatment approach (LeWitt, 2015; Poewe et al., 2010; Warren Olanow et al., 2013), while more recent technological approaches, such as deep brain stimulation (DBS), have been used increasingly as an alternative therapeutic approach. However, both Levodopa treatment and DBS are associated with various side effects and health risks (e.g., invasive neurosurgery in DBS) (Fenoy and Simpson, 2014; Mosley and Akram, 2021). Therefore, exploring alternative approaches to enhance motor-related symptoms is an important step forward to complement current medical and neurosurgical therapies. Such alternatives include virtual and augmented reality-based intervention (Pokharel et al., 2026). For FOG, Cueing, described as temporal or spatial stimuli intended to facilitate and enhance motor execution (Nieuwboer et al., 2007), does not rely on drug intake or invasive operations. Cueing encompasses a range of modalities including auditory, visual, vibrotactile, and internal cueing (Cosentino et al., 2023). The most investigated cueing modalities to date are visual (presented as lines or patterns on the floor) and auditory cueing (e.g., rhythmic sounds or music). Various studies have shown the beneficial effects of these modalities in reducing FOG (Arias and Cudeiro, 2010; Barthel et al., 2018; Delval et al., 2014; Lirani-Silva et al., 2019; Velik et al., 2012; Wang et al., 2021). Neurophysiological evidence indicates that visual and auditory cueing induces alterations in the parietal and occipital brain regions in PD during cued walking (Stuart et al., 2021; Tosserams et al., 2022). However, the presentation of visual and auditory cues may distract users from relevant environmental information (e.g., warning ring of a passing bicycle, interpersonal interactions, or obstacles and uneven terrain). Additionally, users frequently report discomfort due to the visibility of these devices, as they attract attention to their condition, making them more easily recognized and potentially stigmatized in public.

Vibrotactile cueing, a less attention-demanding and discreet method using rhythmic vibrations as external cues, has been shown to improve balance (Ghoseiri et al., 2009) and reduce freezing episodes (Mancini et al., 2018; Rossi et al., 2020). Acute whole-body vibration has also been shown to modulate gait kinematics in people with PD, illustrating the broader potential of vibratory stimulation to influence gait (Oranges et al., 2025). So far, only one study by Stuart and Mancini (2020) investigated the neurophysiological correlates of tactile cueing by use of fNIRS (Stuart and Mancini, 2020). In this study, they reported favorable effects of open (constant rhythmic stimulation) and closed (stimulation based on individual movement) loop tactile cueing on usual walking and turning, but they did not report any changes in brain activation in response to vibrotactile cueing. However, cortical coverage was limited to the PFC. Although the PFC has been implicated in FOG in some studies mentioned above, the effects of vibrotactile cueing likely extend to other brain regions, particularly the parietal and central areas (e.g., SMA), which have also been reported to be involved in FOG (Cockx et al., 2024). Additionally, vibrotactile cueing may not just counteract disruptions in neural pathways associated with FOG, they may also contribute to alternative, compensatory neural pathways that indirectly help attenuate FOG. Given that limited evidence, the effects of cueing, in particular vibrotactile cueing, are not well understood to date.

In summary, research on FOG is lacking both behavioral and neural dimensions characterizing genuine cases of FOG, particularly in more ecologically valid contexts that are closer to everyday scenarios. Furthermore, there is a notable lack of studies investigating the behavioral and neural alterations associated with cueing, and in particular for vibrotactile cueing, one of the most promising modalities of current cueing strategies. In this study, we will therefore investigate the neural mechanisms underlying FOG and vibrotactile cueing in PD. We will take advantage of virtual-reality technology for investigating FOG under more everyday like but highly controlled experimental conditions. Although the main focus of this study is walking-related FOG, 360° turning is also included as an experimental condition, given its status of one of the most potent triggers of FOG and its ability to reliably elicit FOG in laboratory settings (Conde et al., 2023). Neurophysiological (EEG & fNIRS) and movement data (3D motion capture and ground reaction forces) during walking, turning and FOG episodes will be recorded and analyzed.

This research is motivated in particular by the limited evidence on the neural aspects of FOG and how effective countermeasures, such as vibrotactile cueing, can contribute to improvements of FOG related gait disturbances in everyday life. We will use a virtual walking scenario with automatic doorways to induce FOG to address three main research objectives. These objectives will focus on the neural mechanisms and pathways underlying FOG (RO1, RO2) and vibrotactile cueing (RO3). Our first research objective (RO1), aims to identify the cortical brain regions involved in FOG that show differential activation prior to the kinematic onset of FOG compared to normal, unimpaired walking. In the literature, the involvement of various brain regions such as frontal and central areas is reported (Asher et al., 2021; Cao et al., 2021; Handojoseno et al., 2015b; Shine et al., 2014). We expect involvement of similar brain regions (cf. perceptual dysfunction hypothesis (Bardakan et al., 2022)) in our virtual doorway scenario, but we also hypothesize differential activation based on the increased realism and environmental complexity achieved through the use of virtual reality. Second (RO2), we aim to delineate the neural signatures of induced FOG episodes, focusing on the temporal and frequency dynamics within the cortical areas of interest. Based on previous research we are expecting to see FOG specific changes in various frequency bands of interest, including alpha, beta and theta up to 5 s prior to FOG onset (Handojoseno et al., 2012, 2015b; Shine et al., 2014). To this end, we will compare FOG episodes vs. unimpaired walking through virtual doorways. Furthermore, we will analyze the connectivity of these dynamics across the brain regions involved. We expect to observe FOG-related changes in coherence, including increased theta coherence in fronto-central regions as reported previously (Shine et al., 2014).

Lastly (RO3), we aim to investigate whether and how vibrotactile cueing influences the neural patterns associated with induced FOG and contributes to its reduction. We expect that vibrotactile cueing will attenuate the neurophysiological changes linked to FOG (identified in RO2), so that prior to passing doorways, FOG-specific neural signatures will be less pronounced during cued walking than during non-cued walking. Thus, we will evaluate the differential activation patterns of non-cued vs. cued walking through virtual doorways and compare them to FOG specific activation. Additionally, we will assess reductions in the percentage of time spent frozen and analyze corresponding changes in gait kinematics and kinetics.

As part of this research plan, we will consider interindividual differences in FOG kinematics, kinetics, and neural correlates, as well as in the effects of vibrotactile cueing, such as by differential stages of disease, motor symptoms severity, gender, emotional well-being and other well-described moderating factors.

This clinical trial will be performed as a series of confirmatory cross-over studies with people with PD suffering from FOG under the three main research objectives specified above.

## Materials and methods

2

### Study setting

2.1

This study will be carried out at the laboratories of the Institute of Sport and Exercise Sciences of the University of Münster, Germany.

### Eligibility criteria

2.2

Inclusion criteria are: (1) medical diagnosis of idiopathic Parkinson’s disease (Höglinger et al., 2023; Postuma et al., 2015) (2) age ≥ 18 years, (3) Montreal Cognitive Assessment (MoCA) (51) ( ≥ 18, (4) at least one daily freezing episode (reported by participants, assessed via telephone interviews), (5) normal or corrected-to-normal vision and (6) a stable medication for 4 weeks prior to inclusion (Ebersbach et al., 2010).

Exclusion criteria are: (7) previous history of traumatic brain injuries, (8) inability to stand or walk for at least 30 min without walking aids, (9) neuropsychiatric disorders (e.g., depression or anxiety), (10) any medication influencing the nervous system, (11) any severe comorbidities affecting gait, (12) any sensory impairments (e.g., due to polyneuropathy) hampering patients to perceive the vibration of the socks. All criteria are self-reported. Patient’s previous experience with cueing is not an exclusion criterion, but will be assessed as a potential confounding factor.

### Intervention

2.3

Vibrotactile cueing will be applied to ameliorate FOG in PD. A customized vibrotactile cueing device, developed and provided by feelSpace (feelSpace GmbH, Osnabrück, Germany) that is based on a previous prototype as used by Koopman et al. (2019) and Klaver et al. (2023) will be utilized for the open-loop cueing conditions in this study (Klaver et al., 2023; Koopman et al., 2019). Eccentrically rotating mass motors (ERMs) will be used to generate rhythmic vibrations. The intensity of vibrations can be adjusted to the user’s preferences. The frequency ranges from 60 to 260 Hz and increases almost linearly with the voltage (0.6 V to 3.3 V). The vibration actuator will be driven by pulse width modulation and the intensity will be adjustable via API or an App. Increasing the voltage increases both the frequency and the amplitude. The actuator is located medially on the longitudinal arch of each foot, proximal to the calcaneus. The cueing intervention will be applied during walking. Participants will perform two experimental walking blocks. Between the two walking blocks, a break of 10 to 30 min will be provided to prevent exhaustion. Each block includes four walking trials within a virtual environment, each lasting approximately 10 min (cf. Virtual Walking Scenarios). Between trials, perceived physical and cognitive exhaustion are assessed. Cueing (intervention) and non-cueing (control condition) walking trials will be alternated within participants (with the starting condition randomly drawn) and balanced between participants (cf. Participant timeline). Alternation rather than randomization provides the advantage of ensuring balanced trial allocation, even if participants experience fatigue or withdraw earlier than expected. Despite efforts to mitigate fatigue through our experimental design, alternation further ensures an equal number of cued and non-cued trials, minimizing the risk of unequal trial distribution, and ensuring to have available at least one trial per condition. The experimental protocol will be terminated if a participant showed a total of 15 FOG events during non-cued walking (cf. Sample Size).

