On the second day, the session will start with participants being prepared for motion capture by applying reflective markers to the whole body and putting on a safety harness, followed by a short re-familiarization with the treadmill’s self-paced mode. Once comfortable, preparations for neurophysiological measurements will proceed. Participants will be seated and a cap, already equipped with 64 EEG electrodes, will be aligned on their head using anatomical landmarks (nasion, inion and preauricular points). Electrodes will be prepared with gel, followed by preparation of all optodes until adequate signal quality for both EEG and fNIRS is achieved (cf. sections Electroencephalography (EEG) and Functional near-infrared spectroscopy (fNIRS) for detailed information). The experimental procedure will begin with a detailed instruction of the virtual walking task and testing procedure. Participants are then performing a maximum of four walking trials, each lasting roughly 10 min. Before every trial, participants are asked to stand still for 1 min, which will serve as a baseline period for neurophysiological analyses. After each trial, a short break will be administered. If the total number of FOG episodes is below 15 and the patient is reporting a moderate amount of exertion, the next trial will be initiated. Exertion will be assessed using objective measures, including the Rate of Perceived Exhaustion Scale (Borg, 1982) and the Rating Scale Mental Effort (Zijlstra and Van Doorn, 1985). Participants will perform two blocks, each consisting of four walking trials. A break of 10 to 30 min will be provided between both blocks. Cueing and no-cueing will be administered in alternation. After 15 FOG events, the experiment will be stopped after completion of the current trial. The rationale for this design choice is to collect a sufficient number of FOG episodes, while not over exhausting participants. After the walking task 2, further questionnaires regarding the usability and feasibility of the prototype will be handed to the participants (cf. Screenings). For an overview of the whole procedure, see Figure 1. The neurophysiological preparations and measurements will be undertaken by the same personnel described above, who are trained in the preparation and application of various neuroimaging methods.

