### Sample size

2.6

An *a priori* sample size estimation was conducted using G*Power (v.3.1.9.4) for a linear multiple regression, fixed model with R^2^ increase, assuming an alpha level of 0.05, a power of 0.80, one primary predictor, and a total of five predictors (including covariates). We selected a moderate to large effect size of partial R^2^ = 0.25 (i.e., f^2^ = 0.33), informed in part from findings of Handojoseno et al. (2015b) on EEG electrocortical activity changes associated with transitions to FOG episodes (Handojoseno et al., 2015b). Additionally, as we plan to assess multiple FOG trials per person and condition (up to 15 trials) and analyze them using linear mixed effects models, which typically have higher statistical power than traditional aggregated mean analyses, we anticipate achieving sufficient power to detect effects even if they are somewhat smaller than initially estimated. The selection of 15 FOG episodes is driven by Cockx et al. (2024), who reported a median of 15 FOG episodes per participant and observed significant effects on neurophysiological changes, suggesting that up to 15 FOG episodes per participant may serve as a reasonable benchmark for achieving sufficient statistical power in the analyses (Cockx et al., 2024).

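### The 15-FOG stopping rule is worded in conflicting ways, and under either stopping wording alternation does not deliver the equal trial numbers and the minimum of one trial per condition that section 2.3 states

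*Protocol article*

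**What the plan says.** The protocol article describes the limit of 15 in three places.

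- **Section 2.3 (Intervention)** counts non-cued events only: "The experimental protocol will be terminated if a participant showed a total of 15 FOG events during non-cued walking". It gives no time at which the count is checked, and it points to the sample size section.
- **Section 2.5 (Participant timeline)** makes the next trial conditional on a count over all trials, "If the total number of FOG episodes is below 15", together with moderate exertion. It adds: "After 15 FOG events, the experiment will be stopped after completion of the current trial".
- **Section 2.6 (Sample size)** plans for "multiple FOG trials per person and condition (up to 15 trials".

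On balance, section 2.3 alternates the two conditions, "with the starting condition randomly drawn" and balanced between participants. It then says that "alternation further ensures an equal number of cued and non-cued trials", and names as a further benefit "minimizing the risk of unequal trial distribution, and ensuring to have available at least one trial per condition". Sections 2.3 and 2.5 plan two blocks of four trials of about 10 minutes. No section makes stopping depend on both conditions having been run.

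**The concern.** A count of non-cued events and a count of all events reach 15 at different trials, so the staff running a session cannot follow both. The rule decides how much data each participant contributes, and a session that ended under the wrong version cannot be repaired afterwards.

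Alternation alone also does not give the two properties claimed for it. Equal numbers result only if the session ends after an even-numbered trial. At least one trial per condition results only if the session reaches trial 2. The count can end a session before that, and it does so in people who freeze most. They would then have no within-person cued versus non-cued contrast for RO3, the comparison that tests the cueing intervention.

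**Working it through.** **Inputs from the article.** Threshold 15; up to 2 × 4 = 8 alternating trials; random start, so about half of the 30 participants start non-cued; 10 doors and 10 turns of 360° per hospital trial (section 2.8.1.1); testing after 12 hours without medication (section 2.9.2).

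**Not in the article, so assumed.** The number of FOG events per trial and its spread.

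**Step 1: where each rule stops.** Take a constant m events per trial and no cueing effect. Because 2.3 gives no check time, I apply the end-of-trial check of 2.5 to both rules.

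- Rule 2.3 needs k = ceil(15/m) non-cued trials. A non-cued start ends at trial 2k − 1 with k non-cued and k − 1 cued trials. A cued start ends at trial 2k with k of each.
- Rule 2.5 ends at trial t = ceil(15/m), whatever the condition.

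| m | Start | Rule 2.3: last trial (non-cued : cued) | Rule 2.5: last trial (non-cued : cued) |
|---|---|---|---|
| 4 | non-cued | 7 (4:3) | 4 (2:2) |
| 5 | non-cued | 5 (3:2) | 3 (2:1) |
| 8 | non-cued | 3 (2:1) | 2 (1:1) |
| 15 | non-cued | 1 (1:0) | 1 (1:0) |
| 15 | cued | 2 (1:1) | 1 (0:1) |

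The two rules agree in only one of these five cases.

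**Step 2: the two stated properties.** Neither result needs an assumed rate.

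- *Equal numbers.* Under 2.3 the count can reach 15 only in a non-cued trial. Every rule-triggered stop after a non-cued start therefore leaves exactly one extra non-cued trial, and every one after a cued start is balanced. Under 2.5 the extra trial can fall in either condition.
- *At least one per condition.* With 15 or more events in trial 1, a non-cued starter has no cued trial under both rules. A cued starter in the same position has no non-cued trial under 2.5, but always reaches at least 1:1 under the 2.3 count.

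**Step 3: how likely 15 events in trial 1 are.** With Poisson counts, P(15 or more) is below 0.0001 at a mean of 4, 0.017 at 8, 0.083 at 10, 0.228 at 12 and 0.534 at 15. If each of the 20 triggers in a hospital trial can produce one event, it is 0.021 at a 50% chance per trigger and 0.617 at 75%.

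**Step 4: simulated sessions.** No cueing effect, random start, up to eight trials, participant medians of 2, 4 or 8 events per trial with log-normal spread between participants. With log-SD 1 and overdispersed counts (gamma shape 2):

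| Median per trial | 2 | 4 | 8 |
|---|---|---|---|
| One condition missing, 2.3 count | 2% | 5.5% | 13% |
| One condition missing, 2.5 count | 3.5% | 11.5% | 26% |
| Unequal trial numbers, 2.3 count | 14% | 26% | 38% |
| Unequal trial numbers, 2.5 count | 26% | 39% | 52% |

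With log-SD 0.5 and Poisson counts, a missing condition falls to 0% at median 2 and 0.6–1.0% at median 4. Across assumptions the ranges are about 0–12% (2.3) and 0–26% (2.5) for a missing condition, and 7–47% and 26–51% for unequal numbers; runs differ by about one point at the ends. For 30 participants the upper ends for a missing condition are 0.12 × 30 = 3.6 and 0.26 × 30 = 7.8 people.

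**The case against.** **The balance sentences concern fatigue and withdrawal, and strict alternation keeps the difference to one trial.** Both are true. But the sentences claim equality and a minimum of one trial, which is more than a difference of at most one. A participant who stops after trial 1 for any reason has one condition only.

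**The section 2.6 phrase is not a stopping rule.** This is fair. It describes the data expected for analysis, and condition there may not mean cued versus non-cued. It still belongs in the reconciliation, because section 2.3 refers to the sample size section for the limit.

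**The frequencies rest on rates that the document does not give.** This stands. Log-SD 1 turns medians of 2, 4 and 8 into means of about 3.3, 6.6 and 13.2 per trial, which is a strong assumption at the upper end. With little spread and about 4 events per trial, a missing condition is negligible. Only the conflict in wording and the logic of Step 2 are free of assumptions.

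**A reader might infer that the non-cued count biases RO3 towards the hypothesis.** The documents do not support that. The bias arises in unweighted participant means: about +1% to +7% in one set of runs without a cueing effect, and up to +12% in another. Section 2.8.4 plans linear mixed models on the multi-trial data, and section 2.6 prefers these to aggregated means. A random-intercept model on all trials gave −1.7% to +0.4%, and a weighted within-person contrast −4% to −1%. These runs concern FOG counts, whereas the primary outcome is EEG activity and the freezing measure is percentage time frozen.

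**A reader might also infer that the worst freezers drop out of RO3 altogether.** They do not. A mixed model keeps participants with one condition in the fit; what they lack is their own within-person contrast.

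**Conclusion.** The point holds for the text and the design logic. Sections 2.3 and 2.5 state different stopping counts, section 2.6 adds a third wording, and the first two end the same session at different trials. Under neither stopping rule does alternation ensure equal trial numbers or at least one trial of each condition. The absence of any cued trial affects only non-cued starters, about half the sample. The absence of any non-cued trial can follow from the count in section 2.5 but not from that in 2.3.

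The size is uncertain. The ranges in Step 4 depend on the assumed episode rates and spread, and their lower end for a missing condition is zero. Ten doors, ten turns and 12 hours without medication make high counts plausible in severe freezers but do not establish how often they occur. The point does not extend to a biased RO3 estimate under the planned mixed model.

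**What to change.** 1. Reconcile sections 2.3, 2.5 and 2.6 so that one counted quantity and one check time are stated. Which rule to adopt is for the sponsor and the investigators, because section 2.5 gives limiting exhaustion as a reason for the limit alongside collecting enough episodes. No rule is proposed here.
2. Unless the reconciled rule makes them true, withdraw the statements on equal trial numbers and on at least one trial per condition. What alternation itself supports is a difference of at most one trial.
3. Report the number of trials per condition for each participant and the number of participants with only one condition.
4. Keep RO3 on the planned mixed model using all trials. Do not substitute participant means, which can be biased if only non-cued events are counted.

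The cost is wording in three sections and one reporting table. The downside is a less favourable statement about balance.
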